## Abstract

**Background:**

Prophylactic dressings are increasingly used to prevent pressure injuries in hospitalised patients. However, evidence regarding the effectiveness of these dressings is still emerging. This trial aims to determine the clinical and cost-effectiveness of a prophylactic silicone foam border dressing in preventing sacral pressure injuries in medical-surgical patients.

**Methods:**

This is a multicentre, pragmatic, parallel group, randomised controlled trial. A sample size of 1320 was calculated to have >90% power to detect a 5% difference in the primary outcome at an alpha of 0.05. Adult patients admitted to participating medical-surgical wards are screened for eligibility: ≥18 years, admitted to hospital within the previous 36 h, expected length of stay of ≥24 h, and assessed high risk for hospital-acquired pressure injury. Consenting participants are randomly allocated to either prophylactic silicone foam dressing intervention or usual care without any dressing as the control group via a web-based randomisation service independent of the trial. Patients are enrolled across three Australian hospitals. The primary outcome is the cumulative incidence of patients who develop a sacral pressure injury. Secondary outcomes include the time to sacral pressure injury, incidence of severity (stage) of sacral pressure injury, cost-effectiveness of dressings, and process evaluation. Participant outcomes are assessed daily for up to 14 days by blinded independent outcome assessors using de-identified, digitally modified sacral photographs. Those who develop a sacral pressure injury are followed for an additional 14 days to estimate costs of pressure injury treatment. Analysis of clinical outcomes will be based on intention-to-treat, per-protocol, and sensitivity analyses.

**Discussion:**

This trial aims to provide definitive evidence on the effect prophylactic dressings have on the development of hospital-acquired sacral pressure injuries in medical-surgical patients. A parallel economic evaluation of pressure injury prevention and treatment will enable evidence-informed decisions and policy. The inclusion of a process evaluation will help to explain the contextual factors that may have a bearing on trial results including the acceptability of the dressings to patients and staff. The trial commenced 5 March 2020 and has been significantly delayed due to COVID-19.

**Trial registration:**

ANZCTR ACTRN12619000763145. Prospectively registered on 22 May 2019

## Administrative information

Note: the numbers in curly brackets in this protocol refer to SPIRIT checklist item numbers. The order of the items has been modified to group similar items (see http://www.equator-network.org/reporting-guidelines/spirit-2013-statement-defining-standard-protocol-items-for-clinical-trials/).

Role of sponsor {5c}	The NHMRC (sponsor) played no part in study design; collection, management, analysis, and interpretation of data; writing of the report; or the decision to submit the report for publication.

## Introduction

### Background and rationale {6a}

Many hospitalised patients are at high risk of developing pressure injuries (PI). PI onset can be rapid, with injury of skin and/or tissue over bony prominences [1]. Given its anatomical position, the most common location for PI is the sacrum, which is particularly vulnerable to injury and difficult to treat [1]. This is due to pressure and shear that can result from limited mobility and/or long periods of time sitting due to head of bed elevation [1].

A recent meta-analysis found the global prevalence of hospital-acquired pressure injury (HAPI) in adults was 8.4% [2]. HAPI cost approximately US$11 billion in the USA (between the period of 2000 and 2012) (US) [1], £1.4–£2.1 billion in the UK (2011) [3], and in European countries such as the Netherlands up to $2.8 billion annually (USD in 2009) [1]. A 2022 cost analysis of HAPI in Australian public hospitals reported AU $9.11 billion [4]. HAPI have negative consequences for patients in terms of pain [5] and represent a significant economic burden for health services and communities. Therefore, there is increasing emphasis on implementing pressure injury prevention (PIP) strategies. These strategies include risk assessment, support surfaces, nutritional support, repositioning, and moisture and incontinence management, and more recently, prophylactic dressings [6–9]. Preventing HAPI has the potential to save healthcare dollars which can be redirected to other priority areas, free-up hospital beds and improve the overall quality of patient care, outcomes, and experience consistent with national and international priorities.

There is an increasing emphasis on the use of a range of PIP strategies, including the use of prophylactic dressings. These dressings have demonstrated clinical effectiveness in preventing PI in some patient populations and contexts [1, 7, 8]. However, authors of a Cochrane Review updated in 2018 reiterated the certainty of evidence for using dressings in HAPI prevention was low to very low [10]. Since the 2018 Cochrane Review, authors of two high-quality trials of prophylactic silicone dressings have reported positive outcomes but recommend further rigorous testing in clinical practice is needed [11, 12]. Prior to these two studies, rigorous methodological approaches (that is, randomisation, allocation concealment, and blinded outcome assessment via photography) in assessing the feasibility of using prophylactic dressings to prevent PI a general medical-surgical patient population had only been reported in a single pilot study [13].

Cost-effectiveness analyses of prophylactic dressings are sparse. Two within-trial cost-analyses reported prophylactic dressings led to cost savings [14, 15]. The first trial used a retrospective approach to cost analysis that did not include inpatient bed-day costs [15], while the more recent trial calculated an incremental cost-effectiveness ratio based on the average duration of patient admission and expressed as cost per PI avoided [14].

This previous research led us to design a robust randomised controlled trial (RCT) trial to determine the clinical and cost-effectiveness of a prophylactic silicone foam border dressing in preventing sacral HAPI in hospitalised patients assessed at risk for PI. Process evaluation data will also be collected, to evaluate contextual factors (e.g. patient-, provider-, and system-level factors) that may have moderated the effect of an intervention [16].

### Objectives {7}

The primary objectives of the EEPOC trial are to:Determine the clinical and cost-effectiveness of a prophylactic silicone foam border dressing in preventing sacral hospital-acquired pressure injuries (HAPI) in hospitalised patients assessed at risk for PIDescribe the characteristics and clinical care received by patients who develop a sacral HAPI up to 14 days, or until hospital discharge or death after PI occurrenceUnderstand patients and staff perspectives on the use of prophylactic dressing

The primary hypothesis is cumulative incidence (expressed as a percentage) of patients who develop sacral HAPI up to 14 days of admission will be less in patients who are randomly allocated to the routine care plus prophylactic silicone foam dressing group (intervention), compared to patients allocated to routine care only (control).

The secondary hypothesis is patients in the prophylactic dressing group (intervention) will have better outcomes compared to the routine care only group (control) including (1) time to onset of sacral HAPI, (2) incidence of severity of sacral HAPI (based on stage), (3) cost-effectiveness of sacral dressings for the prevention of HAPI, and (4) process evaluation.

### Trial design {8}

This study is a multi-site, parallel group, superiority RCT comparing the effectiveness of a prophylactic silicone foam border dressing in preventing sacral HAPI in hospitalised patients assessed at risk for PI. The unit of randomisation is eligible consenting patients who receive either the prophylactic sacral dressing or the routine care alone. Randomised to either the dressing group or the routine care only group is via a computer-generated 1:1 ratio, in varying permuted block sizes of four, six, and eight, stratified by hospital and division (i.e. medical or surgical).

All patients are followed for up to 14 days or until the trial endpoint, which is development of a new sacral HAPI, hospital discharge, or death—whichever occurs first. Patients who develop a HAPI in either arm are exited from the prevention trial and followed for an additional 14 days until discharge or death—whichever occurs first (up to a total of 28 days) to provide data on PI prevention and treatment costs. This will enable an extended economic evaluation that considers the benefits of prevention in terms of any reduced HAPI treatment costs or HLOS, alongside the costs of prevention.

An integral part of this study is its process evaluation. Process evaluations are particularly important for multi-site trials where it is necessary to determine whether interventions are implemented and received consistently across sites and to understand differences between them [17]. They also provide detailed documentation to enable replication, and information regarding the mechanism of action for significant or non-significant effects, thereby enhancing an intervention’s validity [16, 17].

## Methods: participants, interventions, and outcomes

### Study setting {9}

This multi-site RCT is currently taking place at three acute-care public hospitals in Southeast Queensland, Australia. Two of the hospitals are quaternary hospitals and the third, a tertiary facility. All sites have participated in previous clinical trials. For more details, refer to the Australian New Zealand Clinical Trials Registry: ACTRN12619000763145.

Each site is supported by associate investigator (AI) nurse leaders, who provide ongoing clinical expertise and support for the study. We recruit eligible participants from general medical-surgical wards at each site. The inclusion of multiple sites and wards spreads the recruitment burden and allows testing of the intervention in a variety of acute medical and surgical settings to ensure diverse geographical, unit size, and sub-speciality representation.

### Eligibility criteria {10}

A consecutive sample of all eligible at-risk adult patients admitted to the participating medical-surgical wards are invited to participate in the trial by registered nurse research assistants (ResN). Patients who meet the following inclusion criteria are eligible for recruitment into the sample:

Inclusion criteria:≥18 years of agePatients assessed as being at-risk of HAPI within medical-surgical settings that have been screened within 36 h of hospital admission. ‘At-risk’ is defined as patients with either a completed PI risk assessment (Waterlow Score, or clinical judgement scores of ‘Yes, at risk’ or ‘No, not at risk’) that scores them at-risk of PI, or limited mobility (where human or resource assistance is needed to move), for those who do not have a completed risk assessmentExpected hospital length of stay ≥24h following recruitmentPatient or their proxy able to provide written informed consent

Exclusion criteria:Patients who are unable to be turned (e.g. due to unstable spinal injury)Patients with existing sacral PI, injury, allergy, or lesion in the sacral area at the time of recruitmentPatients with urinary and/or faecal incontinence at the time of recruitmentPatients who are unable to speak or understand English where no interpreter is present at the time of recruitment

### Who will take informed consent? {26a}

ResNs at each site trained in Good Clinical Practice (GCP) screen and recruit participants, obtain their consent, and randomly allocate them to a study group via an independent web-based randomisation service (in accordance with the hospital procedures informed by state governance and international standards). Written informed consent is sought from each patient, family member, or legal guardian (proxy) prior to randomisation.

If consenting participants are allocated to the intervention group, they will be asked to assess their level of satisfaction with comfort of the dressing. They may also be invited to participate in an individual interview conducted by the research assistant to describe their experience of participating in the trial, as part of the process evaluation.

If the participant or their person responsible (i.e. proxy) is unable to read, an impartial witness must be present during the entire consent process. After the patient or their proxy has orally consented to the patient’s participation and has signed the consent form, the witness must also sign and date the consent to attest the information is understood by the patient or their proxy and consent was given freely. Furthermore, where the impairment, disability, or illness is temporary or episodic, an attempt will be made to seek consent at a time when the condition does not interfere with the person’s capacity to give consent.

Participants, their family member, or legal guardian are advised that they can withdraw from the study at any time and that withdrawal will not jeopardise any treatment or relationship with the hospital. A Revocation of Consent form is provided to all participants on enrolment as a means of withdrawal and clearly states that in the event of participant withdrawal, data already collected will be included in the aggregated analysis but that no further data will be collected.

### Additional consent provisions for collection and use of participant data {26b}

As part of the process evaluation that is undertaken alongside the clinical trial [16], it is important that we are able to determine the proportion of eligible patients who refused to participate and describe the demographic characteristics of *both* eligible patients who participated and those who do not (i.e. non-participants). To achieve this, we are collecting demographic characteristics for non-participants, such as age, gender, type of admission (i.e. medical or surgical), and pressure injury risk. Therefore, as part of the consent procedure (i.e. included as an additional tick box in the PICF), eligible patients or their proxy who do not wish to participate will be invited to consent to some non-identifiable information about them being collected by the research team.

In the latter part of the trial, a subsample of patients from the intervention group and nursing staff will be purposively selected to reflect a range of demographic and clinical factors as part of the process evaluation [16]. Nursing staff will be invited to participate following an informed consent process. Research personnel who are involved in the implementation of the trial (such as ResNs and outcome assessors) will also be invited to participate in individual, semi-structured interviews following an informed consent process. The aim of the interviews will be to explore ResN perceptions and experiences of being involved in the EEPOC trial.

## Interventions

### Explanation for the choice of comparators {6b}

The comparator is routine care as per hospital procedures informed by national standards and international practice guidelines [1, 18].

### Intervention description {11a}

#### Intervention: routine care plus dressing

If allocated to the intervention group, participants have a prophylactic sacral dressing applied by a trained research nurse (ResN), following the manufacturer’s instructions. The trial dressing is the Mepilex® Border Sacrum, a foam border silicon dressing available in two sizes to accommodate physical differences of participants. The dressing manufacturer recommends the dressing be changed when the edge begins to roll and/or loses adhesion or becomes soiled. Dressings will also be changed if saturation occurs, if staff accidentally remove the dressing, or if the dressing becomes dislodged.

The ResN takes a baseline photograph of the participant’s sacrum and then applies a silicone foam border dressing (Mepilex®). The dressing and sacral skin are visually inspected every day for up to 14 days. The frequency of dressing replacements (with reason, including device deficiencies) will be documented. Participants in the intervention group will continue to receive routine care, as per hospital procedures informed by national standards and international practice guidelines [1, 18].

#### Control: routine care

Participants allocated to the control group continue to receive routine care according to the hospital procedures informed by national standards and international practice guidelines [1, 18]. Routine care consists of regular skin inspection and assessment, nursing care via use of a pressure redistribution overlay on a standard mattress, or removal of a standard mattress and replacement with a pressure redistributing mattress, possible multidisciplinary review, and second hourly repositioning.

Participants in the control group also have their sacrum photographed every day following recruitment but do not have a dressing applied to the area. Photographs are edited in the same way as the intervention group before being sent to a blinded-to-intervention assessor for evaluation.

### Criteria for discontinuing or modifying allocated interventions {11b}

#### Intervention

Where there is evidence of skin irritation and/or participant-reported discomfort and/or itchiness due to the dressing, the dressing will be removed, the skin reaction reported using standard hospital incident reporting protocols, and the patient exited from the clinical study. Where the patient has developed persistent urinary and/or faecal incontinence, the sacral dressing will be removed, and the patient exited from the clinical study. In our pilot trial, only six participants (5% of the total sample) reported dressing discomfort, due to dressing migration or mild itchiness without any other clinical symptoms of allergic reaction [13].

Note that in either group, diagnosis of a sacral HAPI resulting in the patient exiting the study will be made on a case-by-case basis in consultation with the clinician caring for the patient and/or the team leader. This decision will not influence the assessment of the outcome assessor (i.e. they will not be aware of the decision made by the clinician/team leader). Where there is indecision among the clinical staff caring for the patient regarding the diagnosis of a Stage 1 PI, the assessment by the blinded assessor will be used to determine if the patient should exit the clinical study.

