Digital photography is a novel and practical solution to address blinding. Using study-specific and password-protected iPads, research nurses at each site take high-resolution, de-identified digital photographs of every participant’s sacrum at baseline and each subsequent day they are enrolled in the trial. Photographs are edited using Adobe photo editing software to “blur” surrounding skin to conceal atraumatic skin markings for participants in the intervention group or other markings that may indicate the participant is in the control group (e.g. clothing or bedsheets). Except for the baseline photograph, all modified photos are uploaded into a secure data collection platform and forwarded to a blinded outcome assessor on the same day they are taken. Where a stage 1 (i.e. non-balanceable erythema) is suspected, the patient is be repositioned where possible, the site reassessed after 30 min, and the photograph taken (35). For each photograph, the ResN notifies the blinded outcome assessor as to whether the skin is blanching or non-blanching. The patient exits the clinical study if it is determined they have developed a sacral HAPI which is reported to clinical staff. If the clinical staff caring for the patient diagnose a stage 1 HAPI (even if the blinded assessor did not), the patient is still exited from the study. However, this decision is not disclosed to and therefore does not influence the assessment of the blinded outcome assessor. If the patient has a sacral HAPI, they are included in the estimation of PI treatment costs.

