### Methods in analysis to handle protocol non-adherence and any statistical methods to handle missing data {20c}

All randomised patient data will be analysed by intention-to-treat, regardless of treatment received. However, a per-protocol analysis for trial participants who consented, were randomised, completed the baseline assessment, and had at least one outcome assessment will also be conducted. Where enrolled participants do not have at least one outcome assessment (due to for example unexpected early discharge), they will be defined as “lost to follow-up”, regardless of their time in the trial. While all efforts are made to reduce loss to follow-up, as in most trials, it is inevitable that some missing outcome data may occur. In such circumstances, we envisage using best (no PI) and worst case (PI) scenarios to analyse the impact of missing outcome. These scenarios will form sensitivity analyses to assess the impact of missing outcome data, assuming those missing outcomes had no event or had an event.

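### Removing the dressing for a reaction or incontinence also ends the patient's follow-up for the primary outcome, and the reaction exit can happen only in the dressing arm

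*Protocol article*

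**What the plan says.** Section {11b} of the protocol article (Criteria for discontinuing or modifying allocated interventions), under its Intervention subheading, gives two exit rules. When the dressing irritates the skin, or the participant finds it uncomfortable or itchy, the rule is: "the dressing will be removed, the skin reaction reported using standard hospital incident reporting protocols, and the patient exited from the clinical study". For incontinence: "Where the patient has developed persistent urinary and/or faecal incontinence, the sacral dressing will be removed, and the patient exited from the clinical study". No corresponding rule is given for controls.

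Other sections bear on what exit means:

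- **Trial design {8}:** "All patients are followed for up to 14 days or until the trial endpoint, which is development of a new sacral HAPI". Discharge and death are the other two endpoints, and section {18a} repeats all three.
- **Section {18a}, photography:** photographs are taken "at baseline and each subsequent day they are enrolled in the trial".
- **Consent {26a}:** on withdrawal of consent, "data already collected will be included in the aggregated analysis but that no further data will be collected".
- **Section {20c}:** "All randomised patient data will be analysed by intention-to-treat, regardless of treatment received". Loss to follow-up is defined by the condition "Where enrolled participants do not have at least one outcome assessment". The per-protocol set needs only one outcome assessment. Missing outcomes are to be examined by best-case (no injury) and worst-case (injury) coding.

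**The concern.** Stopping a treatment and stopping outcome measurement are separate decisions, and section {11b} joins them. A dressing reaction is a consequence of treatment, and controls, who have no dressing, cannot have one. So an event caused by the allocated treatment would end outcome collection in that arm alone.

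A patient who exits on day 3 after clean photographs has had an outcome assessment. Section {20c} therefore does not class that patient as lost, and the patient stays in both the intention-to-treat and per-protocol sets, probably as a non-event. Any sacral injury in the remaining days would go unseen in the dressing arm, where the same injury in a control would be recorded. The error favours the dressing, and no later analysis can recover photographs that were not taken.

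**Working it through.** **1. Does exit end outcome collection?** No sentence says outright that photographs stop. Three things point that way. Photographs are scheduled for enrolled days. Exit is the same term used when a pressure injury ends the prevention phase. Post-exit follow-up is described only for patients with an injury (sections {8} and {18a}, and footnote e of Table 1). Dressing removal is not among the endpoints in {8} or {18a}, and it is not withdrawal of consent, the only case for which {26a} stops further data.

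**2. The plan's own sample size.** Inputs from section {14}: 10% against 5%, two-sided alpha 0.05, power 90%. With unpooled variance, n = (1.960 + 1.282)² × (0.10 × 0.90 + 0.05 × 0.95) / 0.05² = 577.9, which gives the stated 578 per group. The total of 1320 gives 660 per arm, used below.

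**3. How many might exit?** Section {11b} reports: "In our pilot trial, only six participants (5% of the total sample) reported dressing discomfort". That implies a pilot of 6 / 0.05 = 120. If it was randomised 1:1 (an assumption), the dressing arm had 60, and 6 / 60 = 10%. These were reports of discomfort, not recorded exits. I use exit fractions f of 5% and 10%, with 2% as a low case.

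**4. Bias under no true effect, reaction exits only.** Assumptions: 10% risk in both arms; exited patients at average risk and kept as non-events; a share L of their risk falls after exit, taken as 50% or 75% (the document gives no figure).

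- Observed dressing-arm risk = 0.10 × (1 − f × L)
- Injuries missed = 660 × 0.10 × f × L, out of 66 expected
- Chance of a significant result favouring the dressing = Φ(d / SE − 1.96), where d = 0.10 × f × L, SE = √(2 × p̄ × (1 − p̄) / 660), and p̄ is the mean of the two observed risks

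| f | L | Observed risk | RR | Missed | False benefit |
|---|---|---|---|---|---|
| 2% | 50% | 0.0990 | 0.990 | 0.66 | 2.9% |
| 2% | 75% | 0.0985 | 0.985 | 0.99 | 3.1% |
| 5% | 50% | 0.0975 | 0.975 | 1.65 | 3.5% |
| 5% | 75% | 0.0963 | 0.963 | 2.48 | 4.2% |
| 10% | 50% | 0.0950 | 0.950 | 3.30 | 4.9% |
| 10% | 75% | 0.0925 | 0.925 | 4.95 | 6.7% |

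The nominal one-directional rate is 2.5%.

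**5. If incontinence exits are also confined to the dressing arm.** Let a fraction fi exit for incontinence with risk ri. The remaining patients have risk r0 = (0.10 − fi × ri) / (1 − fi), and observed risk = 0.10 − f × r0 × L − fi × ri × L.

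- Low (f = 0.05, L = 0.5, fi = 0.01, ri = 0.10): r0 = 0.100, observed risk 0.0970, RR 0.970, false benefit 3.8%.
- High (f = 0.10, L = 0.75, fi = 0.05, ri = 0.20): r0 = 0.0947, observed risk 0.0854, RR 0.854, false benefit 14.8%.

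If one rule covers both arms, this part roughly cancels.

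**6. If exits are instead treated as missing.** Between best-case and worst-case coding, 33 exits move the dressing-arm risk by 33 / 660 = 5 percentage points and 66 exits by 66 / 660 = 10 points. The design difference is 5 points.

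**The case against.** The strongest reply is that the effect is small and partly inferred. The article never says that photographs stop, and exit does not end all data collection: patients with an injury are followed further and length of stay is recorded for everyone. Exited patients can still be analysed in their randomised arm, so intention-to-treat is not literally broken. Coding as non-events is an assumption, and an unseen analysis plan may handle partial follow-up. The Kaplan-Meier, log-rank and Cox analyses and the rate per 1000 bed days can censor at exit. The pilot reports were of dressing migration or mild itchiness, and a dislodged dressing is changed under section {11a}, so not every report would become an exit. At the planned 5% dressing-arm risk, the reaction-only assumptions miss 0.8 to 2.5 of 33 injuries and move RR from 0.50 to about 0.49–0.46, which would not change the conclusion.

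Much of this stands as a limit on size. The figures depend on assumed exit rates, post-exit risk and coding. The one-sided incontinence case is conditional: faecal incontinence is listed among the complications collected daily without restriction to an arm, so the sound request there is for clarification.

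It does not remove the defect. No other reading of exit is supported for a patient without an injury. The time-to-event and rate analyses are secondary, and they assume that exit is unrelated to risk. Best- and worst-case coding bounds the missing outcomes too widely to settle the question if exits reach 5–10%. Intention-to-treat needs outcomes after treatment stops as well as the right arm label.

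**Conclusion.** The concern holds. Section {11b} sets a rule that conflicts with the follow-up in {8} and {18a} and undercuts the analysis promised in {20c}. For reactions, the loss of outcome data falls on the dressing arm alone.

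The likely bias from reactions is modest: RR 0.975–0.925 under no true effect, with 1.7–5.0 of 66 injuries missed, and close to nil at 2% exits. It could reach RR 0.85 only if incontinence exits are also one-sided and the high assumptions hold together. All of these sizes rest on non-event coding and on exit and risk figures that the article does not give. This should be fixed because the error runs in the direction of the hypothesis, cannot be repaired at analysis, and is cheap to prevent. Confidence in the size is medium.

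**What to change.** In section {11b} and the SOP, separate stopping the dressing from stopping follow-up:

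- Keep the clinical rule for removing the dressing.
- After removal for any reason, continue daily photographs and blinded assessment until sacral injury, discharge, death or day 14, unless consent is withdrawn.
- State one incontinence rule that applies to both arms.
- Analyse these patients in the arm to which they were randomised.

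The cost is a protocol and SOP amendment plus some extra photographs, each of which must be edited and assessed. Research nurses already photograph participants daily, and the sample size is unchanged. The article describes recruitment as still open, so the change helps only patients whose dressing is removed after the amendment; those already exited should be counted and reported by arm.
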